## Abstract

**Objective::**

Tripterygium wilfordii multiglycosides has been demonstrated to be effective in reducing proteinuria and alleviate edema in patients with chronic kidney disease. We aim to evaluate its efficacy and safety in idiopathic membranous nephropathy.

**Methods and analysis::**

This is an randomized, open-labeled, controlled clinical trial. Twenty eligible patients with idiopathic membranous nephropathy will be randomly assigned into the intervention group and the control group at a rate of 1:1. Patients in the intervention group will receive tripterygium wilfordii multiglycosides tablets (1–1.5 mg/kg body weight/d, orally) in addition to the original treatment of angiotensin converting enzyme inhibitor/angiotensin receptor blocker, while the control group will continue with the original treatment of angiotensin converting enzyme inhibitor/angiotensin receptor blocker. The treatment course is 6 months, and clinical variables of patients will be measured at baseline and each monthly follow-up. The primary efficacy outcome measure is absolute decrease in urinary protein quantity after 6 months of treatment compared with baseline at randomization. The secondary efficacy outcome measures include absolute decrease in urine albumin-creatinine ratio in spot urine after 6 months of treatment compared with baseline at randomization, the percentage of patients who reached effective clinical response, and the percentage of patients who developed composite renal endpoint. Safety outcome measures include incidence of adverse events, incidence of serious adverse events, and death.

## Introduction

1

Idiopathic membranous nephropathy (IMN) is one of the common pathological types of primary nephrotic syndrome in adults, with a peak age around 40 to 50 years old.^[1,2]^ In China, IMN accounts for 30.2% of primary glomerular disease and is the leading cause of nephrotic syndrome in adults over 40 years old.^[3]^ Immunosuppressive therapy is the current first line treatment of IMN, and its efficacy has been confirmed by a large number of high-level evidence.^[4]^ For IMN patients who have moderate to low risk for progressive renal function decline, the latest version of Kidney Disease: Improving Global Outcomes guideline of Chronic Glomerular Disease^[5]^ still recommends a “wait and see” policy in addition to treatment of angiotensin converting enzymes inhibitor (ACEi) or angiotensin receptor blockers (ARB). However, we have found a considerable number of patients with proteinuria below 3.5 g/d suffered from significant edema symptom, making the supporting treatment of full-dose ACEi/ARB alone less well accepted in this population, especially in the elderly.

Tripterygium wilfordii multiglycosides is extracted and purified from the root xylem of *Tripterygium wilfordii* Hook F (TwHF), which is a member of the Celastraceae family of perennial vine-like plants.^[6]^ It has been reported in literature and also shown by our experience that tripterygium wilfordii multiglycosides can reduce proteinuria and alleviate edema symptom of patients with chronic kidney disease,^[7–9]^ through mechanisms including but not limited to activating T cells^[10]^ and regulating nuclear factor κB pathway.^[7,10,11]^ Most experience of tripterygium wilfordii multiglycosides in IMN so far came from observational studies with limited number of subjects. There is still a lack of solid evidence to support its use in IMN patients.

This is a randomized, open-label, controlled trial to investigate the efficacy and safety of tripterygium wilfordii multiglycosides in IMN patients who would be classified as moderate to low risk according to Kidney Disease: Improving Global Outcomes guideline. The results might be used to improve our understanding of this drug in treating IMN and provide evidence for clinical practice. We hypothesized that tripterygium wilfordii multiglycosides combined with ACEi/ARB is superior to ACEi/ARB alone in treating IMN.

## Methods and analysis

2

### Study design

2.1

This is a single center, open-label randomized controlled clinical trial following superiority trial design, and is sponsored by Nephrology Department of Sichuan Provincial People's Hospital. A flowchart of the trial design is shown in Fig. 1. The study has been approved by the Ethics Committee of Sichuan Provincial people's Hospital (No. 2021.325–1), and registered on Chinese Clinical Trial Registry (Identifier# ChiCTR2100048382).

**Figure 1 F1:**
[figure not shown]
Flowchart of the trial. m = months, RASi = renin-angiotensin system inhibitors, TW = tripterygium wilfordii multiglycosides.

### Patients

2.2

Patients diagnosed as IMN by renal biopsy will be included in this study. Twenty eligible IMN patients will be randomly assigned to an intervention group and a control group at a rate of 1:1, with 10 patients in each group. Patients in the intervention group will receive tripterygium wilfordii multiglycosides tablets on the basis of ACEi/ARB treatment, while patients in the control group will continue with ACEi/ARB treatment. The study duration will be 6 months, during which clinical data and samples will be collected according to a visit schedule at each follow-up.

### Inclusion criteria

2.3

Patients should meet all following criteria to be considered eligible: has no evidence of secondary membranous nephropathy; age between 18 and 75 years old; has 24-hour albuminuria between 1.0 and 3.5 g after at least 3 months of standard dose of ACEi/ARB treatment; estimated glomerular filtration rate (eGFR) >60 mL/min/1.73 m^2^ according to Chronic Kidney Disease Epidemiology Collaboration formula using the latest serum creatinine value at screening; and agrees to voluntarily participate in the study and signs an informed consent form.

### Exclusion criteria

2.4

Patients with any one of the following criteria will be excluded: has received glucocorticoids or other immunosuppressants in the past 6 months; has any clinical evidence of secondary membranous nephropathy (tumors, drugs, other autoimmune diseases such as systemic lupus erythematosus, etc); has any of the following comorbidities including chronic liver disease, myocardial infarction, stroke, uncontrolled hypertension and diabetes, malignant tumor; is known to allergic to tripterygium wilfordii multiglycosides or has contraindications for use; female patients who are pregnant (or intend to be pregnant within half a year), breastfeeding or unwilling to take contraceptive measures; has an expected life expectancy <6 months; is currently participating or have participated in other clinical trials within 3 months; refuses to sign an informed consent form or be unable or unwilling to comply with research protocol approved by the researcher; has any other conditions which the researchers believe makes the subject unsuitable for this study.

### Randomization

2.5

A random number list has been generated by the first author ([name]) using SPSS version 24.0 (IBM Corporation, Chicago, Illinois, USA) using simple randomization method. Eligible patients will be randomly assigned to the interventional group or the control group at a rate of 1:1 by the number inside a concealed envelope containing random codes according to the order of enrollment. The concealed envelopes have been prepared by an irrelevant researcher.

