### Sample size

2.10

In a preliminary screening from January 2010 to December 2017 in our center's Renal Treatment System, a total of 87 IMN patients were identified. The average amount of proteinuria in this population was 2.89 ± 0.62 g/d at the time of diagnosis. According to the clinical data of our center, combined with the published data on proteinuria in IMN patients, we expect that the experimental treatment is superior to the control when mean decrease in proteinuria in the intervention group is 2.0 g/d higher than that in the control group. Therefore, the sample size calculated with type I error of 0.05 (bilateral) and a randomization ratio of 1:1 to provide a power of 80% to detect an effect size of 2 g/d is 9 per group. The total number increased to 20 considering a loss of follow-up rate of 10%. Minimum loss to follow-up is expected given such small sample size and intensive clinic visits during follow-up. Therefore, 20 subjects will be included in this study.

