It should be noted the calculated sample size is rather small, only 10 for each group considering a loss of follow-up rate of 10%. Thus, strict adherence to study protocol is of great importance to the success of this trial and every effort to keep the patient being followed up as planned. Our department is a core member of China's Chronic Kidney Disease Management Center and has an sophisticate electronic system which combines the advantages of on-site and remote health management to track our patients. The system sends mobile messages to patients who are close to their appointed visits to remind them to show up at clinic. We also have a designated nurse to manage patients’ follow up. All these measures aim to keep patients in regular follow up. In addition, 4 authors of this work are all senior nephrologists. With the help of our CKDMC's management, we will try every effort to achieve a maximum compliance and minimum loss of follow up rate in this study.

In summary, this study aims to provide scientific evidence for tripterygium wilfordii multiglycosides in treating IMN through a randomized, open-labeled, controlled clinical trial. The results may provide evidence to support treatment of tripterygium wilfordii multiglycosides in IMN, and hopefully have important significance for clinicians who are to make therapeutic decisions.

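### Simple randomisation of 20 patients does not guarantee the stated 10 per group (10:10 has a 17.6% chance), and the list was generated by the first author of an open-label, single-centre trial

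*Protocol article*

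**What the plan says.** All references are to the protocol article.

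- **Group sizes (section 2.2, Patients).** Patients are "randomly assigned to an intervention group and a control group at a rate of 1:1, with 10 patients in each group". The Discussion repeats the figure: "only 10 for each group considering a loss of follow-up rate of 10" percent.
- **Sample size (section 2.10).** The number needed "to provide a power of 80% to detect an effect size of 2 g/d is 9 per group". It is raised for 10% loss to follow-up: "Therefore, 20 subjects will be included in this study".
- **Method (section 2.5, Randomization).** The list was made "using SPSS version 24.0 (IBM Corporation, Chicago, Illinois, USA) using simple randomization method". No block, stratum or fixed arm total is mentioned.
- **Who made the list (section 2.5).** "A random number list has been generated by the first author". Allocation then uses concealed envelopes in order of enrolment, and a researcher outside the trial prepared them.
- **Setting (section 2.1, Study design).** One centre, open-label.

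The article does not say who enrols patients, who opens the envelopes, or who keeps the list after it was made.

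**The concern.** The plan has two separate weaknesses here.

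**Group sizes.** In its usual meaning, simple randomisation assigns each patient independently with probability one half. Equal arms are then only one possible outcome, and in a trial of 20 not a likely one. Sections 2.2 and 2.10 nevertheless treat 10 per group as given, and the power statement is made for 9 evaluable per group. An uneven split costs some power and could leave few patients on the study drug, in a trial that also aims to describe its safety.

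**Custody of the sequence.** Envelopes hide the next code from those who see only envelopes. They do not hide it from the person who made the list, who here belongs to the trial team. Sections 2.4 and 2.9 let the researchers exclude or withdraw patients on their own judgement. If someone with that discretion knew the sequence, patients could be steered. With about 10 per arm, one or two steered patients could matter. The covariance analysis on baseline proteinuria (section 2.11) would not correct selection on prognosis that is not measured.

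**Working it through.** **1. The plan's own figure.** Inputs from section 2.10: difference 2 g/d, two-sided alpha 0.05, power 80%, ratio 1:1, loss 10%. The only SD given is 0.62 g/d, and it describes proteinuria at diagnosis, not its change.

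- The step for loss reproduces: 9 / (1 − 0.10) = 10 per group, 20 in total.
- The 9 per group does not follow from SD 0.62: the formula gives 2 (normal) or 3 (t) per group. With 0.62 × √2 = 0.877, it gives 4 or 5. That is a separate matter and is not argued here.
- To study power by split, I therefore solved for the SD that gives 80% at 9:9 with the noncentral t. It is 1.42 g/d, a standardised difference of 2 / 1.42 = 1.41. This is an assumption and is not in the document.

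**2. Split under simple randomisation.** Let X be the number allocated to the drug, X ~ Binomial(20, 0.5). No SD is needed.

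- P(10:10) = C(20,10) / 2^20 = 184,756 / 1,048,576 = 17.6%.
- P(one arm below 9, that is 8:12 or worse) = 2 × 263,950 / 1,048,576 = 50.3%.
- P(7:13 or worse) = 2 × 137,980 / 1,048,576 = 26.3%.
- P(6:14 or worse) = 2 × 60,460 / 1,048,576 = 11.5%.
- One-sided, for exposure to the drug: P(X ≤ 6) = 11.5% / 2 = 5.8%.

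**3. Power by split.** Two-sided t test with n1 + n2 − 2 degrees of freedom and noncentrality 1.41 / √(1/n1 + 1/n2).

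| 20 analysed | Power | 18 analysed | Power |
|---|---|---|---|
| 10:10 | 84.5% | 9:9 | 80.0% |
| 9:11 | 84.1% | 8:10 | 79.5% |
| 8:12 | 83.0% | 7:11 | 78.0% |
| 7:13 | 81.0% | 6:12 | 75.2% |
| 6:14 | 77.8% | 5:13 | 70.9% |
| Binomial average | 82.4% | Binomial average | 77.5% |

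The average cost is 84.5 − 82.4 = 2.1 points with 20 analysed and 80.0 − 77.5 = 2.5 points with 18. The average for 18 takes the analysed patients as Binomial(18, 0.5), so loss is assumed unrelated to arm.

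**4. Range over the SD.** If the SD of change were 0.62, power would exceed 99.9% even at 5:13. At 0.877 it would be 98% at 5:13. The power cost is visible only if the SD of change is near the value that the plan's 9 per group implies.

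**5. Predictability of a fixed 10/10 list.** Someone who sees past allocations and always guesses the arm with more codes left expects 10 + (2^20 / C(20,10) − 1) / 2 = 10 + (5.68 − 1) / 2 = 12.3 correct guesses of 20. Under simple randomisation the figure is 10.

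**The case against.** Simple randomisation is valid. It does not bias the estimate, the t test holds with unequal arms, and in an open-label trial it has the merit that past allocations predict nothing. Section 2.5 says the list already exists, so its split is already settled. If it was made by ranking 20 random numbers and cutting at 10, the arms are as section 2.2 says and only the label is loose. This stands: the article cannot show which case applies, so the supportable request is to reconcile the two sections.

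A reader might infer from the 50.3% that the trial has an even chance of being underpowered. The documents do not support that. Nine per arm is the requirement for equal arms, not a floor for each arm. Under the assumed SD, with 20 analysed, power stays above 80% down to 7:13 and falls below it only at 6:14 or worse, an 11.5% chance.

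A reader might also infer that concealment has been broken. The text does not show this either. Envelopes are concealed, used in order of enrolment and prepared by someone outside the trial, and nowhere is the first author said to enrol or treat patients or to keep the list. Selection would need the list's author to enrol patients or to pass the sequence on. Those roles may be set out in the full protocol. What remains is that a member of the trial team generated the sequence, and the envelopes cannot hide it from that person.

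**Conclusion.** The point holds in a limited form. Sections 2.2, 2.10 and the Discussion rely on group sizes that the method in section 2.5 does not guarantee. It would be too strong to say that 10:10 will not occur: it has a 17.6% chance, about one in six. The binomial figures rest only on reading simple randomisation in its usual sense.

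The average loss of power is small, about 2 to 2.5 points, and depends on an SD of change of 1.42 g/d that the document does not state. The inconsistency itself and the tail of badly unequal splits matter more than the average.

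The origin of the list is a risk to concealment, reduced in part by the envelopes. It is not a demonstrated breach.

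**What to change.** 1. Reconcile sections 2.2 and 2.5. If the existing list contains exactly 10 codes per arm, replace the word simple with a correct description of how it was made.
2. If it does not, replace it with a restricted list that reaches 10:10 at 20 patients, preferably permuted blocks of varying size that together sum to 20 and are not disclosed to enrolling staff. One random permutation of 10 and 10 codes would also fix the totals.
3. Have the statistician mentioned in section 2.11, or the uninvolved researcher who prepares the envelopes, generate and hold the list. Nobody who enrols or treats patients should have access, and section 2.5 should say so.
4. If enrolment has started, keep the allocations already made and build the list for the remaining patients so that the arms end as near 10:10 as possible.

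The cost is a new list, new envelopes and one amended paragraph. The downside is predictability: because allocations are visible in an open-label trial, some late ones become easier to guess (about 12.3 of 20 correct under one fixed permutation, against 10 under simple randomisation), and the last is then certain. That is why undisclosed varying blocks and independent custody belong with the change.

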### Interventions

2.6

All patients will have received ACEi/ARB treatment for at least 3 months before enrollment. After randomization, patients in the interventional group will receive tripterygium wilfordii multiglycosides tablets (1–1.5 mg/kg body weight/d, orally, divided to 3 times) in addition to their ACEi/ARB treatment, and patients in the control group will proceed with their original ACEi/ARB treatment. The overall treatment duration is 6 months. During the study period, existing treatments for concomitant medical conditions are permitted and should be recorded in details.

### Outcome measurement

2.7

#### Efficacy outcomes

2.7.1

Primary efficacy outcome is absolute decrease in proteinuria after 6 months of treatment compared with baseline at randomization.

Secondary outcomes include: absolute decrease in urine albumin-to-creatinine ratio (ACR) after 6 months of treatment compared with baseline at randomization; the percentage of patients who have achieved complete response, defined as proteinuria less than 0.3 g/d and serum albumin ≥3.5 g/dL; the percentage of patients who have achieved partial response, defined as a decrease in proteinuria ≥50% compared with the level at randomization.

#### Safety outcomes

2.7.2

Since the major adverse effects of tripterygium wilfordii multiglycosides are liver dysfunction and gonadal suppression,^[12,13]^ we will closely monitor manifestations of these 2 aspects in addition to routine practice on safety surveillance. Therefore, safety outcomes in this study will include but not limited to the following:

Clinical: blood pressure, edema, anemia, menstruation status in the women;Blood biological tests: complete blood cell count; serum creatine, albumin, alanine aminotransferase, aspartic aminotransferase, total bilirubin, direct bilirubin, indirect bilirubin, lactate dehydrogenase.

An adverse events (AE) mean any adverse event that happens during the study duration, regardless of its relevance to the experimental intervention. Any adverse event happens will be recorded in details and followed up until resolution. Serious AE includes life-threatening conditions, hospitalization, prolonged hospitalization, transient or permanent disability, and death. Any serious AE should be reported to the sponsor within 24 hours after occurrence, recorded, and followed as AE.

### Data collection and management

2.8

All enrolled patients will have their first visit at the time of screening, the second visit at randomization and be followed up at the end of each month afterwards (Table 1). In addition, there will be 1 follow up at 2 weeks after randomization (Visit 3), whose main purpose is to closely monitor potential adverse effect of tripterygium wilfordii multiglycosides. The overall duration of treatment will be 6 months. At each follow-up as shown in Table 1, the medical history will be enquired, and blood and urine tests will be carried out in the central lab in Sichuan Provincial People's Hospital with standardized methods.

**Table 1 T1:** Visit schedule of this study.

Research program	Screening	Randomization				Clinic visit			
Visit number	1	2	3	4	5	6	7	8	9
Visit day	−14 (±7)	0	14 (±3)	30 (±3)	60 (±3)	90 (±3)	120 (±3)	150 (±3)	180 (±3)
Informed consent	√								
Inclusion/Exclusive criteria	√	√							
Random assignment		√							
Demographics	√								
Medical history	√	√	√	√	√	√	√	√	√
Physical examination	√	√	√	√	√	√	√	√	√
Vital signs	√	√	√	√	√	√	√	√	√
Blood lab tests		√	√	√	√	√	√	√	√
Urine lab tests		√	√	√	√	√	√	√	√
Collect blood and urine samples		√			√		√		√
Pregnancy test	√	√							
Combined medication		√	√	√	√	√	√	√	√
Adverse events		√	√	√	√	√	√	√	√
Drug distribution		√	√		√	√	√	√	
Drug compliance reminder		√	√		√	√	√	√	

In this study, the paper version of CRF table will be used for data collection, RedCap online database will be used to manage data, double input comparison method will be used for data entry and verification, and corresponding data verification and cleaning will be carried out. During the study period, the principle researchers will check the trial data monthly to ensure internal consistency and data integrity.

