### Withdraw criteria

2.9

Patients with any of the following conditions will be withdrawn from this study: being found having any of the exclusive criteria after enrollment; takes glucosteroids or other immunosuppressants during the study; has intolerable side effects of drugs; has any serious adverse event that makes subjects unsuitable for continuation, such as severe infection, uncontrollable hyperglycemia, and/or hypertension; the patient asks to withdraw; other situations which the researchers believe makes the patient not appropriate to continue.

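### Table 1 stops pregnancy testing at day 0, although five of the six drug distributions come later, so a pregnancy on treatment may be recognised late or first read as a drug effect

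*Protocol article*

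**What the plan says.** Table 1 in section 2.8 of the Protocol article sets out nine visits, from screening (day −14) to day 180. Three of its rows matter here:

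- "Pregnancy test": visits 1 and 2 only (days −14 and 0).
- "Drug distribution": visits 2, 3, 5, 6, 7 and 8 (days 0, 14, 60, 90, 120 and 150).
- "Urine lab tests": every visit from 2 to 9.

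Section 2.4 excludes "female patients who are pregnant (or intend to be pregnant within half a year), breastfeeding or unwilling to take contraceptive measures". Section 2.9 withdraws a patient on "being found having any of the exclusive criteria after enrollment", which covers a pregnancy that begins during treatment. Treatment lasts six months (section 2.6), and patients aged 18 to 75 are eligible (section 2.3).

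Section 2.7.2 states that "the major adverse effects of tripterygium wilfordii multiglycosides are liver dysfunction and gonadal suppression" and lists "menstruation status in the women" among the clinical safety outcomes. The Discussion ranks menstrual disorder as one of the two foremost side effects. Table 1 collects history, physical examination and adverse events at every visit after randomization, and section 2.7.2 adds: "Any adverse event happens will be recorded in details and followed up until resolution".

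**The concern.** The exclusion and withdrawal rules show that the authors do not want the drug taken in pregnancy. The ban on intending pregnancy within half a year matches the length of treatment. A withdrawal rule works only if the event is detected, and scheduled testing ends on the day the first tablets are handed out.

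After that, the routine signals are what the woman reports and whether her periods continue. The second signal is weak for this drug, because a missed period is also an expected adverse effect. Nothing in the article asks for a pregnancy test before amenorrhoea is attributed to gonadal suppression.

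Two things are at stake. A participant who becomes pregnant may be given more drug before the pregnancy is recognised. Her amenorrhoea may also be recorded at first as gonadal toxicity, which is a safety outcome the trial sets out to watch.

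**Working it through.** The protocol gives no figure of its own to reproduce on this point. The check is a count of Table 1, followed by simple arithmetic.

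**1. Visits and tests.** Visits after day 0 are visits 3 to 9, which is 7. Pregnancy tests among them: 0. Distribution visits: 6. Those with a same-day test: visit 2 only, so 1 of 6, and 5 of 6 have none.

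**2. Drug supply handed out without a same-day test.** Assumption: each distribution covers the time to the next one (the article does not say so).

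| Distribution | Nominal days covered | Test that day? |
|---|---|---|
| Visit 2 (day 0) | 14 − 0 = 14 | yes |
| Visit 3 (day 14) | 60 − 14 = 46 | no |
| Visits 5 to 8 (days 60 to 150) | 4 × 30 = 120 | no |
| Total | 180 | |

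Without a same-day test: 46 + 120 = 166 days, and 166/180 = 92%.

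**3. Interval without a scheduled test.** From day 0 to day 180 this is 180 days. It is not the likely delay in recognition, because history and adverse events are reviewed about monthly. If recognition is one or two visits late (assumption), the further drug exposure is 1 × 30 = 30 to 2 × 30 = 60 days.

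**4. Expected number of pregnancies.** Assumptions, neither in the article: 0 to 5 of the 10 drug-arm patients are women who can become pregnant, and contraception fails in 1% to 10% per year.

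Expected pregnancies = women × yearly failure × 0.5 year

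- Low end: 0 × 0.01 × 0.5 = 0
- Middle example, 2 women at 5%: 2 × 0.05 × 0.5 = 0.05
- High end: 5 × 0.10 × 0.5 = 0.25

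The required contraception, and the peak age of about 40 to 50 given in the Introduction, point to the lower part of this range.

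**5. With tests added at visits 4 to 9.** Tests would fall on days 0, 30, 60, 90, 120, 150 and 180. The longest nominal gap is 30 days. With the ±3-day windows it is at most (60 + 3) − (30 − 3) = 63 − 27 = 36 days. Supply handed out on a test day becomes 14 + 120 = 134 of 180 days (74%). The 46-day supply from visit 3 would have a test at day 30, which is 30 − 14 = 16 days into it.

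**The case against.** The case for leaving the schedule alone is that this is a choice of monitoring intensity and contradicts nothing. Women must use contraception, two tests guard entry, and history, examination and adverse events are collected at all seven later visits. Menstruation status is a named outcome, and section 2.7.2 promises close monitoring of gonadal effects on top of routine surveillance, with a list that is open-ended. An experienced nephrologist may well test a woman who reports a missed period, and a rule for such tests could sit in the full protocol. The 92% figure also applies a same-day standard that the article never sets, and the proposed change would still leave 180 − 134 = 46 days (26%) short of it.

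Much of this stands. No rule is contradicted, lasting misattribution is unlikely, the expected number of cases is small, and the interval between tests is a better measure than the 92%. A rule for tests prompted by symptoms may exist elsewhere.

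The central point is not answered. The article prints a complete visit schedule with its own pregnancy-test row, and that row ends at day 0, so the timing of scheduled tests is fixed here and not left to another document. The safeguards listed depend largely on self-report and menstruation, and the protocol itself says that the drug disturbs menstruation.

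**Conclusion.** The concern holds. As printed, Table 1 schedules no pregnancy test while the drug is being taken, and the withdrawal rule in section 2.9 therefore has no scheduled test behind it. The counts (0 of 7 later visits, 5 of 6 distributions) come straight from the table and need no assumption.

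The consequence is limited. It concerns the safety of a few possible participants: perhaps 30 to 60 further days of drug in a case recognised one or two visits late, with 0 to 0.25 such pregnancies expected. These ranges rest on the assumed number of women, contraceptive failure rate and delay. No decision rule depends on the count, and the efficacy analyses and sample size are unaffected. The change is worth making because the possible harm is serious and the remedy costs very little.

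**What to change.** For women who can become pregnant, extend the pregnancy-test row of Table 1 to visits 4 to 9 (days 30 to 180), using a urine test. At visits 5 to 8, do the test before the drug is dispensed. Visit 3 (day 14) can be left out, because it closely follows the day 0 test and visit 4 checks the supply it hands out. Add one sentence to section 2.7.2: a pregnancy test is to be done before a missed period is attributed to gonadal suppression.

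The cost is an amendment to one table row plus that sentence, and a urine test at visits that already include urine work. With up to 5 such women per arm this is at most 5 × 6 = 30 tests in the drug arm, or 10 × 6 = 60 if the control arm is tested too. No visit is added. The downside is the small price of the tests and an occasional false positive that has to be repeated.
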